## **Purpose**

- To investigate whether CYP test guided treatment improves antipsychotic drug treatment in patients with schizophrenia compared to clinical dose titration.
- To investigate whether intensified clinical monitoring focusing on tolerability, effectiveness and patient's perception of medical treatment can improve antipsychotic drug treatment in patients with schizophrenia compared to control.
- To compare the effect of CYP test guided treatment and intensified clinical monitoring on antipsychotic drug treatment in patients with schizophrenia.

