## **Design**

A prospective blinded randomized trial designed as parallel study with three study arms; two intervention arms and one control arm. The study duration is 12 months. Outcome measures are recorded at baseline and 12 months follow up.

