## **Primary outcome measures:**

- a. Time to discontinue of initial antipsychotic drug treatment.
- b. Persistence for treatment, i.e. percentage of patients remaining in treatment within a defined time period

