### **Data processing**

Data comparisons are made both between the two study arms, but also between the subgroups of extreme and normal metabolizers in each study arm. Due to the unpaired and presumably nonparametric character of our data, we plan to use Mann-Whitney's rank sum test, chi squared test and log rank test hypothesis testing. For continuous data, ANOVA is used. The level of significance is 5%. Since the selected power measurements are interdependent, it is not necessary to correct for the risk of mass significance.

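### Dependence between the outcomes does not justify waiving multiplicity control, and it does not touch the three arm comparisons or the genotype groups

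*Protocol*

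**What the plan says.** Under Data processing, the protocol sets one level for all testing ("The level of significance is 5" per cent) and then waives adjustment: "Since the selected power measurements are interdependent, it is not necessary to correct for the risk of mass significance". I read the measurements in that sentence as the outcome measures; the word before it looks like a translation slip.

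The tests this covers are set elsewhere:

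- **Outcomes.** Primary outcome measures lists two, with no order or success rule: "Time to discontinue of initial antipsychotic drug treatment" and "Persistence for treatment, i.e. percentage of patients remaining in treatment within a defined time period".
- **Arms.** Design describes a "parallel study with three study arms; two intervention arms and one control arm".
- **Comparisons.** Purpose gives three: "To investigate whether CYP test guided treatment improves antipsychotic drug treatment in patients with schizophrenia compared to clinical dose titration"; whether intensified monitoring "can improve antipsychotic drug treatment in patients with schizophrenia compared to control"; and "To compare the effect of CYP test guided treatment and intensified clinical monitoring".
- **Genotype groups.** Data processing adds comparisons involving extreme and normal metabolizers in each arm. It also speaks of two arms where the design has three.

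Study Population bases the sample size on extreme metabolizers, at an unadjusted 5% level, and names time to discontinuation as the primary outcome for that purpose. No hierarchy, gatekeeping or division of alpha appears anywhere in the protocol.

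**The concern.** The waiver is an explicit decision with a stated reason, so it is not a detail left for a statistical analysis plan. A plan that followed the protocol would inherit it.

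The reason fails twice. First, two positively dependent tests at 5% have a joint error above 5% unless they are in effect the same test. Second, the argument concerns outcomes only. It says nothing about testing three pairs of arms, or about testing again by genotype.

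According to Publication and Target group for the project, the results feed a Medical Technology Assessment read by specialists, politicians and hospital administrators. They would take 5% as the chance of a false primary claim, and the protocol does not say to which claim or set of claims that 5% applies.

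**Working it through.** **1. The plan's own figure that uses this alpha.** Study Population gives d0 = 45 days, SD = 39.3, type 1 error 5%, type 2 error 10%, and a result of 19.5, rounded to 20 per arm.

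- Variance ratio: 39.3²/45² = 0.7627.
- Usual formula: 2 × (1.960 + 1.282)² × 0.7627 = 16.0, i.e. 17. The exact t-test gives 17.05, i.e. 18.
- With the beta term read as two-sided: 2 × (1.960 + 1.645)² × 0.7627 = 19.8, i.e. 20.

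The stated number is therefore reproduced approximately, and it contains no allowance for multiplicity.

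**2. Does dependence restore 5%?** Two outcomes with correlation rho, one arm comparison, two-sided 5% each, no true effect, 1,000,000 simulated sets of normal test statistics. The protocol gives no rho, so it was ranged.

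| rho | chance of at least one p<0.05 |
|---|---|
| 0 | 9.8% |
| 0.5 | 9.1% |
| 0.8 | 7.8% |
| 0.9 | 7.0% |
| 1 | 5.0% |

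Only perfect dependence with a single comparison returns 5%.

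**3. Add the three arm comparisons.** Six independent tests would give 1 − 0.95⁶ = 26.5%. Allowing for arms that share data (same method, two outcomes by three comparisons):

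| rho | one population | arm comparisons in each of two genotype groups | three overall arm comparisons plus extreme versus normal within each arm |
|---|---|---|---|
| 0.5 | 21.3% | 38.0% | 40.9% |
| 0.8 | 18.4% | 33.5% | 36.1% |
| 0.9 | 16.7% | 30.6% | 33.1% |
| 1 | 12.2% | 23.1% | 24.7% |

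The last two columns are two readings of the subgroup wording. The bottom row grants the protocol's argument in full, and 12.2% remains from the three comparisons alone.

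**4. With the trial's own structure.** Null trials were simulated with 3 arms of 100 (20 extreme, 80 normal, from Recruitment, randomization). Assumptions not in the protocol: exponential times with median 365 days (50% persistence at 12 months), and persistence judged at 12 months. Both outcomes come from the same event times, so their dependence is built in. The ranges cover separate runs of 4,000 to 5,000 trials.

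| Tests counted | chance of at least one p<0.05 |
|---|---|
| One arm comparison, log-rank and chi-squared | about 6% |
| Three pairwise log-rank tests | 12-13% |
| The same plus three persistence tests | 15-16% |
| The same plus arm comparisons in extreme metabolizers | 24-25% |
| The same plus arm comparisons in normal metabolizers | about 29% |

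Secondary outcomes are not counted.

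**5. A possible remedy for three arms.** A global log-rank at 5%, with pairwise log-rank tests at 5% read only if it is significant, gave about 5% in the same null trials. Its price, with an assumed hazard ratio of 0.65 for the CYP arm against control: power for that comparison falls from about 52% to 42% if the monitoring arm equals control, and from about 51% to 38% if monitoring lies between the two.

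**The case against.** The strongest reply has four parts.

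- **The sentence concerns outcomes, and there the practical cost is small.** Both primary outcomes derive from the same event times, and one comparison with both gives about 6% instead of 5%. This stands. Most of the inflation comes from the arm comparisons and genotype groups, which the sentence does not address.
- **Three purposes need not form one family.** A genetic test and a monitoring programme are different interventions, and leaving each unadjusted against control is a recognised position. This stands as a possible choice, but the protocol does not argue it. It would not cover two unordered primary outcomes or the subgroups.
- **The protocol already points to one primary outcome.** Study Population calls time to discontinuation the primary outcome. A reader might infer that a claim on either outcome alone would count as success, but no such rule is written. Equally, Primary outcome measures lists two with no order, so the matter is open.
- **The subgroup figures depend on a reading.** Taken literally, the wording means extreme versus normal within an arm. The sample size section instead suggests arm comparisons among extreme metabolizers. Nothing clearly plans a confirmatory test in normal metabolizers. The 24-29% therefore illustrates one reading and is not a property of the plan.

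**Conclusion.** The justification for the waiver is incorrect and should not govern the primary inference. The error is about 6% for a single comparison with both primary outcomes, 12-13% for three pairwise log-rank tests taken as one family, and 15-16% when persistence is added. These figures assume no true effect, 100 per arm and 50% persistence at 12 months. The direction does not rest on the simulated event times: ranging the correlation from 0 to 1 leaves 12.2% or more for three comparisons.

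A reader might infer that any positive claim would carry several times the stated 5%. The documents do not support that. It applies to a trial-wide family that includes the genotype groups, which the protocol neither defines nor excludes, and a single claim on a single comparison is affected far less. What does hold is that the reason given is false and that no confirmatory family is fixed to which the 5% could apply.

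**What to change.** 1. Delete the sentence on mass significance.
2. Make time to discontinuation the single primary outcome, in line with Study Population, and persistence a supportive one.
3. Name the confirmatory comparisons and their order, and say whether the three purposes are one family or separate questions, with the reason. Correct the reference to two arms and state which genotype contrast is meant.
4. State where the extreme-metabolizer comparison sits in that order. The trial is sized on it, so making it exploratory would change the basis of the sample size.
5. Label all other subgroup and secondary tests exploratory.

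If the three pairwise comparisons are treated as one family, the global log-rank followed by pairwise tests at 5% is valid for three arms and needs no division of alpha. The protocol should state its cost: roughly 10-13 percentage points of power for a single pairwise comparison in the cases simulated.

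If the extreme-metabolizer comparisons stay confirmatory under a Bonferroni split instead, the protocol's own inputs show the cost. With n = 20, power is Φ(45/(39.3 × √(2/20)) − z) = Φ(3.621 − z), where z is the two-sided critical value. That gives 95.2% unadjusted (z = 1.960), 89.0% for three tests (z = 2.394; 21 per arm would restore 90%) and 83.7% for six (z = 2.638; 24 per arm).

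Steps 1 to 5 need no extra patients in themselves. Their downside is that persistence and unlisted subgroup p-values lose confirmatory status.

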### **Target group for the project**

Professional, political, and organizational decision makers, i.e. specialists in psychiatry, politicians and hospital administrators.

### **Publication**

The project is designed as a PhD project and will be published as PhD thesis. In addition, parts of the project will be included in the Medical Technology Assessment "Does dose individualization by genotyping improve the drug antipsychotic treatment?". Both positive and negative results of the experiment will be published. Decisions on authorship and co-authorship on all publications that originate from this project will be made in accordance with the Vancouver Recommendations.

### **Ethical considerations**

Prior to the start-up of all project-related activities, approvals are obtained from the Scientific Ethics Committee. All patient-related information is recorded in an anonymized form and handled in accordance with

the Act on Processing of Personal Data and the Act on Patients' Legal Status. Relevant scientific ethical guidelines are followed. The trial is reported to the Danish Data Agency.

The CYP test is based on a single blood sample and without further disadvantages for the patient. The CYP test is fully implemented at Sct. Hans Hospital and the clinical guideline for use and interpretation of the CYP test results has been thoroughly tested in a highly specialized clinical setting. The CYP test is used only for dose guidance and has no influence on the patient's disease prognosis, illness or death. Therefore, the test is not expected to create significant ethical problems in relation to the patient. Since the clinical effect of genotyping compared to the clinical dose titration is unknown, the randomization to a study arm were CYP test results cannot be used for drug choice or dose management is not expected to involve ethical problems for the patient or the treating physician. Moreover, the trial intervention is not associated with risks or disadvantages for the patient.

#### **Project organization and finances**

The project was initiated by [name], [name] and [name] and received financial support from The Danish National Board of Health and TRYG Fonden. There is no financial link between researchers and private companies, foundations, etc., with interests in the outcome of the research project in question.

All funding is administered by the Finance Department, Bispebjerg University Hospital and used for salaries and administrative expenses. No money is paid to patients participating in the trial.

The project is part of a Medical Technology Assessment (HTA), an interdisciplinary assessment of the clinical,

237 economic and socio-cultural effects of a routine use of the genetic test in psychiatry. The project is a  
238 collaboration between the Clinical Pharmacological Unit and Psychiatric Department E at the Bispebjerg  
239 University Hospital, Copenhagen, the Research Institute of Biological Psychiatry at the Sct. Hans Hospital in  
240 Roskilde and the Danish Health Institute (DSI) in Copenhagen.  
241

242

## Appendix 1 Guidance on the use of the CYP test in the dosing of the drug treatment (11)

### Predicted phenotype

### Clinical Guide

Normal metabolizer (EM) of CYP2D6:

- Standard dose of CYP2D6 dependent preparations
- No difference between CYP2D6 dependent and independent preparations

Slow metabolizer (PM) of CYP2D6:

- Observation of adverse reactions of CYP2D6 dependent medicinal products
- Regular determination of serum concentration
- Lower dosage of CYP2D6 dependent drugs than the standard dose
- Switch to CYP2D6 independent preparations

Fast metabolizer (UM) of CYP2D6:

- Observation for the lack of efficacy of CYP2D6 dependent drugs
- Regular determination of serum concentration
- Higher dosage of CYP2D6 dependent drugs than the standard dose
- Switch to CYP2D6 independent preparations

Normal metabolizer (EM) of CYP2C19:

- Standard dose of CYP2C19 dependent drugs
- No difference between CYP2C19 dependent and independent preparations

Slow metabolizer (PM) of CYP2C19:

- Observation of adverse reactions of CYP2C19 dependent drugs
- Regular determination of serum concentration
- Lower dosage of CYP2C19 dependent drugs than the standard dose
- Switch to CYP2C19 independent preparations
